**Figure 1 figure1:**
[figure not shown]
Flowchart of this study. K-MoCA: Montreal Cognitive Assessment (Korean version); MMSE-K: Mini-Mental State Examination (Korean version).

**Table 1 table1:** Overall procedure of this study.

			Study period		
Time point			Visit 0 (screening)		Visit 1
**Enrollment**					
	Eligibility screen	✓			
	Informed consent	✓			
	Randomization and allocation	✓			
**Intervention**					
	Verum acupuncture group			✓	
	Sham acupuncture group			✓	
**Assessment**					
	Demographics	✓			
	Medical history	✓		✓	
	MMSE-K^a^	✓			
	K-MoCA^b^	✓			
	CRIq^c^			✓	
	fNIRS scan^d^			✓	
**Safety**					
	Vital sign	✓		✓	
	Adverse events			✓	

^a^MMSE-K: Mini-Mental State Examination (Korean version).

^b^K-MoCA: Montreal Cognitive Assessment (Korean version).

^c^CRIq: Cognitive Reserve Index Questionnaire.

^d^fNIRS: functional near-infrared spectroscopy.

### Participants and Recruitment Strategy

#### Eligibility Criteria

The inclusion criteria for healthy controls (the group without cognitive impairment) are as follows: (1) males and females aged ≥19 years without cognitive impairment (MMSE-K≥24, K-MoCA≥23); (2) participants without severe neurological, organic dysfunction; and (3) participants or authorized surrogates who voluntarily sign the informed consent.

The inclusion criteria for the group with cognitive impairment are as follows: (1) males and females aged ≥60 years showing cognitive impairment (MMSE-K<24, K-MoCA<23) or diagnosed with mild cognitive impairment (MCI) or dementia with a clinical dementia rating<3; (2) participants or authorized surrogates who voluntarily sign the informed consent; and (3) participants who can complete this study.

The exclusion criteria for healthy controls (the group without cognitive impairment) are as follows: (1) participants with other brain disorders, alcoholism or drug abuse, neuropsychiatric disease, or taking psychiatric medicines, and severe organic dysfunctions inducing cognitive impairment; and (2) participants with any other reasons that may be considered inappropriate by the researcher.

The exclusion criteria for the group with cognitive impairment are as follows: (1) severe dementia patients with a clinical dementia rating of 3; (2) patients with other brain disorders such as cerebrovascular disease and epilepsy; (3) patients with cognitive impairment induced by another primary disease; (4) patients with severe organic dysfunctions; (5) patients presenting alcoholism or drug abuse, with neuropsychiatric disease or taking psychiatric medicines; and (6) patients with any other reasons that may be considered inappropriate by the researcher.

#### Enrollment, Randomization, and Blinding

Recruitment will be conducted through advertisements on websites and public announcements. Promotion through local communities is also under consideration. The recruitment of participants with cognitive impairment will be promoted through cooperation with community dementia care centers. In this study, in accordance with the recruitment of the participants, the effect of age on brain function will also be investigated; therefore, recruitment in the group without cognitive impairment will not be restricted to older adult participants.

Stratified block randomization will be performed according to sex. Both groups will be assigned in a 1:1 ratio to the study and control groups by applying a block size of 4. Randomization will be conducted using a computer-generated allocation list by an assigned researcher not involved in the assessment or intervention. Participants will be blinded to the type of intervention used. The practitioner will not provide clues regarding allocating information to the participants during the study. Blinding will be maintained until the end of the study. Participants will be asked about their experience of blinding after the end of the study.

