**Methods:**

This study is a randomized, placebo-controlled trial. Participants without (n=30) and with cognitive impairment (n=30) will be randomly assigned to the verum or sham acupuncture groups. The verum acupuncture group will receive acupuncture stimulation at acupoints related to cognitive function and gain deqi sensation. The sham acupuncture group will receive superficial needling at nonacupoints not related to cognitive function. Each group will undergo cognitive function tests, functional near-infrared spectroscopy imaging before and after acupuncture stimulation, and an assessment of CR. The primary outcomes will be differences in resting brain activities according to disease status, differences in resting brain connectivity before and after acupuncture stimulation between the 2 groups, and changes in brain activity in relation to the CR index. The secondary outcomes will be brain connectivity or network metrics associated with CR and differences in neural activity between the cognitive task and resting states.

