## Methods

### Trial Design, Setting, and Aim

This study will be a single-center, block-randomized, placebo-controlled, parallel-group clinical trial. The study will be conducted at the College of Korean Medicine at Sangji University. This protocol complies with the SPIRIT (Standard Protocol Items: Recommendations for Interventional Trials) guidelines [25]. The aim of this study is to investigate the acute neural mechanisms of acupuncture stimulation concerning CR and to identify the neural substrates of CR in the group without cognitive impairment and the group with cognitive impairment using fNIRS.

The participants will be divided into 2 equal groups: the verum acupuncture group (study group) and the sham acupuncture group (control group). After each group is confirmed to participate in the study through screening (visit 0), fNIRS scanning and acupuncture manipulation will be conducted at visit 1. Cognitive function assessments, including the Korean version of the Mini-Mental State Examination (MMSE-K) and Montreal Cognitive Assessment (K-MoCA), will be conducted during screening. At visit 1, each participant will be measured twice using fNIRS (first and second scan) before and after acupuncture stimulation. Finally, CR marker assessment, such as the Cognitive Reserve Index Questionnaire (CRIq), will be conducted through interviews in visit 1. The period between visit 0 and visit 1 will not exceed 1 week. Participant recruitment was initiated on August 22, 2023, and the study is scheduled to continue until February 2025. The flow chart is illustrated in Figure 1, and the overall procedure is presented in Table 1.

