### Interventions

In the study group, verum acupuncture stimulation will be conducted for 15 minutes by stainless steel acupuncture (0.25 mm×40 mm, Dongbang acupuncture) on acupoints, which are known to be associated with cognitive functions in previous studies (Baihui [GV20], Sishencong [EX-HN1], Taixi [KI3], Zusanli [ST36], Hegu [LI4], and Taichong [LR3]), and deqi sensation will be induced [24,34,35]. The needle will be lifted and thrust approximately 30-50 mm and twisted and rotated at approximately a 90°-180° angle 60 times/minute (60 Hz). The manipulation will then be performed at 1-minute intervals to maintain the amount of stimulation and achieve deqi sensation. A questionnaire on deqi sensations will be implemented.

For the control group, superficial needling acupuncture (depth of needling: 1-2 mm per nonacupoint) will be performed for 15 minutes using stainless steel acupuncture (0.25 mm×40 mm, Dongbang acupuncture) on nonacupoints. Nonacupoints, which are not related to cognitive function, would be approximately 1 cm away from the acupoints of the study group. The needles for sham acupuncture will remain in place. In the case of superficial needling, manipulation techniques and induction of deqi sensation will not be achieved.

Superficial needling can be a subtype of minimal acupuncture [36]. We thought that the characteristics of acupoints, depth of acupuncture stimulation, intensity of the stimulation, and deqi sensation would all be determinants of acupuncture stimulation. Therefore, we selected minimal acupuncture that lacks these features as a sham control. This type of sham acupuncture has been applied in various studies, including Bell’s palsy, migraine, and chronic musculoskeletal pain syndrome, for a long time [37-40].

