#### Dropout Criteria

The participants will be excluded in the following cases: severe adverse events occur; difficulty proceeding with the trial due to adverse events; the participant or a legal representative wants to stop the trial; the participant withdraws consent to join the trial; the participant fails to finish the interview or the fNIRS scan; and progression of the trial is considered inappropriate by the principal investigator.

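### One fixed block size of 4 at a single centre would let unblinded staff who track assignments predict up to about 31% of them with certainty: an avoidable, though not demonstrated, risk of selection bias

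*Protocol article*

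**What the plan says.** The section Enrollment, Randomization, and Blinding gives the method in two sentences: "Stratified block randomization will be performed according to sex", and then "Both groups will be assigned in a 1:1 ratio to the study and control groups by applying a block size of 4". Trial Design, Setting, and Aim adds the setting: "This study will be a single-center, block-randomized, placebo-controlled, parallel-group clinical trial". The abstract gives the numbers: "Participants without (n=30) and with cognitive impairment (n=30) will be randomly assigned to the verum or sham acupuncture groups".

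The allocation list is computer-generated and run by a researcher who takes no part in assessment or intervention. On blinding, the article says "Participants will be blinded to the type of intervention used". The MMSE-K, K-MoCA and CRIq assessors are blinded as well. The practitioner is asked only to give participants no clues.

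Under Interventions, the two arms look different to the person needling. In the verum arm needles are lifted, thrust and rotated, and "The manipulation will then be performed at 1-minute intervals to maintain the amount of stimulation and achieve deqi sensation". In the sham arm needles go in 1-2 mm and are left alone.

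Entry includes an open-ended judgement. In the cognitively impaired group, for example, the exclusions cover "patients with any other reasons that may be considered inappropriate by the researcher".

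**The concern.** With blocks of 4 at 1:1, each block holds two verum and two sham places. Once two of one arm have been used, the rest of the block is determined. Keeping the list with a separate researcher protects the list itself. It does not stop the sequence being rebuilt from treatments already given, if someone sees those treatments, knows the block size and can sort participants by stratum. Sex is the stated stratum and is visible. Small fixed blocks are weakest where delivery cannot be blinded and all assignments occur at one site.

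Verum versus sham is the only randomised contrast in the trial; disease status and cognitive reserve are not assigned. If knowledge of the next arm affected who was accepted or when a person was booked, the arms could differ before any needling. Blinding the participants would not correct that.

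**Working it through.** **Inputs.** Block of 4 at 1:1 within sex strata (Enrollment, Randomization, and Blinding). Planned total 30 + 30 = 60 (abstract). Female share so far 70% in the impaired group and 57% in the unimpaired group (Results). The article gives no predictability figure, so there is none to reproduce.

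**Assumptions.** The sex mix so far continues, giving 21 women and 9 men in the impaired group and 17 and 13 in the unimpaired group. The article does not state whether cognitive status has its own lists, so both cases are computed. The observer knows the block size and every earlier assignment in the stratum, in order.

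**One block.** Two verum and two sham places can be ordered in 6 equally likely ways.

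| Position | P(next is certain) | P(best guess correct) |
|---|---|---|
| 1 | 0 | 0.500 |
| 2 | 0 | 0.667 |
| 3 | 1/3 | 0.667 |
| 4 | 1 | 1.000 |
| Mean | 4/3 ÷ 4 = 33.3% | 2.833 ÷ 4 = 70.8% |

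**Projected to 60.**
- Four lists (21, 9, 17, 13): complete blocks 5 + 2 + 4 + 3 = 14, with one participant left over in each list. Certain: 14 × 4/3 = 18.7, and 18.7/60 = 31.1%. Best guess correct: 14 × 2.833 + 4 × 0.5 = 41.7, or 69.4%.
- Two lists (38, 22): complete blocks 9 + 5 = 14, with two left over in each. Certain: again 18.7, or 31.1%. Best guess correct: 14 × 2.833 + 2 × (0.5 + 0.667) = 42.0, or 70.0%.
- Other plausible sex splits: 28.9% to 33.3% certain.

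**If the observer is one assignment behind.** Table 1 places randomisation at visit 0, and treatment follows at visit 1 up to a week later. If the latest assignment in the stratum is not yet delivered, only position 4 can be certain, and only when the first two assignments match (probability 1/3). This gives 14 × 1/3 = 4.7, and 4.7/60 = 7.8%. With two undelivered the share is 0%.

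**How often that happens.** Sixty people over about 78 weeks (August 2023 to February 2025) is 60/78 = 0.77 per week, or 0.19 per week in each of four lists and 0.385 in each of two. If arrivals are random, the chance that the previous person in the list entered within the last week is 1 − exp(−0.19) = 17% to 1 − exp(−0.385) = 32%. The lag would therefore be the less common case, although clustered recruitment would make it more frequent.

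**With varying blocks.** Blocks of 4 and 6 in random order were simulated against an observer who knows the two possible sizes and updates after each assignment. About 6% of assignments were certain (5.7% for a list of 30), and the best guess was correct 67-69% of the time. A longer fixed block helps much less: 25% certain for a fixed 6 and 20% for a fixed 8.

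**The case against.** The strongest reply is that foreknowledge needs both a knower and a route, and the article establishes neither. It says that a Korean medicine doctor performs the needling. It does not say that one person treats everyone, knows the block size or has any part in screening or enrolment. The list is held independently, the screening tests are scored by a blinded investigator, and the open-ended exclusion belongs to the researcher, not the practitioner. How assignments are released may well be set out in the full protocol. All of this stands. A reader might infer that the practitioner knows every past assignment, or that 31% of assignments are in fact known. The text supports neither: 31% is close to the ceiling for a fully informed observer.

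A reader might also count the withdrawal rule under Dropout Criteria ("progression of the trial is considered inappropriate by the principal investigator") as a second route. It operates after randomisation, when the participant's own assignment already exists, so predicting the next one plays no part.

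Nor can a size of bias or an inflated type I error be read from the plan. Any such figure would need an assumed shift in who is accepted. It would also rest mainly on best-guess accuracy, which varying blocks barely change.

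Finally, little remains to be changed. Results reports 50 of 60 enrolled, with the unimpaired group already at 30. That leaves 30 − 20 = 10 impaired participants, or about 10 × 1/3 ≈ 3 assignments that could be certain. This limits the value of a change. However, Quality Control allows further recruitment once the target is met, and the limitations section speaks of enlarging the sample.

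What survives is narrower: a single fixed size of 4 is a stated choice, not an omitted detail, and it is more predictable than it needs to be where delivery is unblinded.

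**Conclusion.** The point holds as a minor design weakness. Up to about 31% of assignments (29-33%) could be predicted with certainty by unblinded staff who know the block size and follow assignments by stratum. The share is about 8% when the latest assignment in the stratum is still undelivered. The figures assume that the sex mix so far continues; the 31% is the same with two lists or four. The documents do not show that such staff exist or that they influence entry, so this is an avoidable risk to the verum-sham comparison and not evidence that it is biased.

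**What to change.** For all participants not yet randomised, including any additional recruitment under Quality Control, replace the block size of 4 with randomly varying sizes (for example 4 and 6) that are not disclosed to the practitioner or to recruiting and screening staff. State that the list researcher releases each assignment only after the eligibility decision has been recorded.

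The gain is the removal of most certain knowledge, from about 31% to about 6%. Best-guess accuracy hardly moves (about 70% to 67-69%), so the timing of release matters as much as the block sizes.

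The cost is a short amendment and a regenerated list from the researcher already assigned, with no extra visits or participants. Those already randomised keep their assignments. End-of-list imbalance within a stratum can rise from at most 2 to at most 3, counted from the start of the new list. A block of 4 still open at the switch should either be completed, in which case its last places stay predictable, or be cut short, which can leave up to 2 more.

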#### Sample Size

In this study, the number of participants has been determined statistically. In our hypothesis, the significance level (α) and power (1–β) will be set to 5% and 80%, respectively. Then, an effect size will be calculated using an estimated value of the variability in the MMSE-K and K-MoCA scores based on the literature [26]. As a result, the number of samples came out to be about 10-15 for each group (study or control group) to satisfy the criteria of the normal deviates of significance level and power in the healthy controls and patient groups. The anticipated dropout rate was set to 10%. A similar number of subjects (i.e., 10–15 subjects in each group) can be found in the previous neuroimaging studies [27-29].

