### Statistical Analysis

Only data from participants who completed the fNIRS scan, cognitive function test, and measurement of CR will be contained in the statistical analysis. All categorical data are presented as frequencies or percentiles and will be analyzed using the chi-square or Fisher’s exact test. All numerical data will be presented as the mean and standard deviation and analyzed using an independent *t* test or Wilcoxon rank-sum test. Preprocessing and analyses of fNIRS data will be performed using MATLAB and the NIRSIT analysis tool.

A two-sample *t* test will be performed to compare the brain activations and connectivity between the groups with and without cognitive impairment. A paired *t* test will be conducted to compare the brain activations and connectivity before and after acupuncture stimulation. The CR values from CRIq will be applied for correlation analysis in the form of continuous variables or divided into binary groups (high and low CR) by mean values for subgroup analysis. Since the expression of CR may appear differently depending on the disease status, a subgroup analysis will be conducted by dividing the healthy control and the patient group. Mixed model analysis will be adjusted to determine the interaction effect of intervention and CR in both groups. Pearson correlation will determine the CR-related brain connectivity or clinical score–related metrics. If there is a significant age difference between 2 groups, the age factor will be added as a covariate in the analysis to adjust the effect of age as much as possible.

Statistical significance in fNIRS imaging would be explored using uncorrected and corrected levels (false discovery rate and family-wise error). At the uncorrected level, uncorrected *P*<.001 will be used, and at the corrected level, *P*<.05 will be applied.

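### Allocation is stratified by sex, but no planned test or model carries sex, so a verum–sham comparison gives up some power to the extent that sex predicts the pre–post change (minor)

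*Protocol article*

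**What the plan says.** **Allocation.** Under Enrollment, Randomization, and Blinding: "Stratified block randomization will be performed according to sex". Then: "Both groups will be assigned in a 1:1 ratio to the study and control groups", in blocks of 4. Sex is the only stratum named. The groups assigned to study and control can hardly be the two arms themselves. They are most naturally the impaired and unimpaired groups, each planned at 30 in the Abstract. That reading implies separate lists by disease group, but the text does not say so.

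**Outcome.** In Outcome Measures, the second primary outcome is the before-to-after difference in brain activation, compared between verum and sham.

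**Analysis.** The Statistical Analysis section names:
- a two-sample t test between disease groups;
- a paired t test that "will be conducted to compare the brain activations and connectivity before and after acupuncture stimulation";
- for interaction with cognitive reserve (CR): "Mixed model analysis will be adjusted to determine the interaction effect of intervention and CR in both groups";
- an independent t test or rank-sum test for numerical data in general;
- a subgroup analysis that separates healthy controls from patients.

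The one covariate rule is that age enters if the two groups differ significantly on it. Sex appears nowhere in that section.

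**The concern.** Stratifying on a factor makes the arms alike on it, so the verum–sham difference varies less from trial to trial than under simple randomisation. An analysis that omits the factor does not see this: the variance the factor explains stays in the residual, and the standard error describes a noisier design than the one used. If the factor is prognostic, the test rejects too rarely and power is given away. With about 10–15 participants per arm in each disease group, precision is scarce.

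The covariate rule does not help. It makes adjustment depend on a significance test of imbalance and leaves out the one factor that allocation is stated to use. Where the disease groups are pooled, disease status raises the same issue, and there it also matters whether it was a stratum.

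**Working it through.** **1. The plan's own figure.** The Sample Size section says "the significance level (α) and power (1–β) will be set to 5% and 80%, respectively" and that "an effect size will be calculated using an estimated value of the variability in the MMSE-K and K-MoCA scores", but gives no effect size or SD, so 10–15 per arm cannot be reproduced. It can be back-solved (two-sided test assumed): n = 2(1.96 + 0.8416)²/d² = 15.70/d².
- n = 10: d = √(15.70/10) = 1.25 (1.33 with the noncentral t).
- n = 15: d = √(15.70/15) = 1.02 (1.06 with the noncentral t).

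**2. Inputs for the check.** One disease group has 30 participants, 15 per arm. Blocks of 4 are formed within sex. The impaired group's mix is 21 women and 9 men (70% female so far, from the Results section, applied to 30). The effect is 1.06 within-sex SDs, which 15 per arm detects with 80% power. R², the share of outcome variance explained by sex, is **an assumption**, taken from 0 to 0.30.

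**3. Formula.** With within-sex SD of 1 and arms balanced within sex, the true sampling SD of the verum–sham difference is about √(4/30) = 0.365. The unadjusted standard error is about 0.365/√(1 − R²). At R² = 0.20 that is 0.365/0.894 = 0.408; at 0.30 it is 0.365/0.837 = 0.436.

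**4. Simulation** (4,000 trials per setting; two-sample t test against a linear model with arm and sex):

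| Assumed R² of sex | SE by formula | SE, unadjusted | True SD of estimate | Type I error, unadjusted | Power, unadjusted | Power, adjusted |
|---|---|---|---|---|---|---|
| 0 | 0.365 | 0.362 | 0.367 | 0.052 | 0.806 | 0.802 |
| 0.02 | 0.369 | 0.366 | 0.363 | 0.052 | 0.795 | 0.797 |
| 0.05 | 0.375 | 0.372 | 0.363 | 0.042 | 0.790 | 0.806 |
| 0.10 | 0.385 | 0.385 | 0.369 | 0.046 | 0.757 | 0.791 |
| 0.20 | 0.408 | 0.407 | 0.371 | 0.032 | 0.728 | 0.802 |
| 0.30 | 0.436 | 0.438 | 0.373 | 0.024 | 0.675 | 0.803 |

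SEs and SDs are from the runs with an effect. The power difference is about 0, 0, 2, 3, 7 and 13 points. Simulation error on each power is about √(0.8 × 0.2/4000) = 0.6 points, so the first two rows show no loss.

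**5. Pooled disease groups.** With 60 participants, strata of sex by disease group (17/13 and 21/9 women/men), an effect of 0.736 SD and 3,000 trials per setting, the joint R² of both factors was set at 0, 0.05, 0.10, 0.20, 0.30 and 0.50. Unadjusted power is 0.79, 0.79, 0.77, 0.71, 0.65 and 0.47. Adjusted power stays at 0.79–0.81.

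**6. What counts as loss.** Steps 4 and 5 hold the within-stratum SD fixed. If the total SD is fixed instead, with 60 participants, a 0.65 SD effect and joint R² of 10%, 25% or 40%, unadjusted power is 70%, 72% or 74% and adjusted power is 74%, 82% or 89%. A conventional t-test calculation gives 69.7%. On that scale the loss is a gain not taken.

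All figures concern the verum–sham contrast. They do not carry over directly to the intervention-by-CR interaction.

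**The case against.** **Disease group is not ignored.** A reader might infer that the analysis carries neither stratification factor. It does not go that far: the Statistical Analysis section analyses controls and patients separately, and the Sample Size section gives its number per arm within each. Inside one disease group that factor is constant and cannot inflate a standard error. This stands, and it confines the disease-group part to a pooled contrast. Such a contrast is not excluded, because the second primary outcome is not restricted to one disease group and the split is called a subgroup analysis.

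**The paired t test has no verum–sham standard error.** This stands. The point bears on the mixed model and on any between-arm t test, not on the paired test. That the second primary outcome lacks a clearly named between-arm test is a separate matter.

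**The loss is not certain.** This stands. No R² is given, and in a pre–post difference stable sex differences in level largely cancel. As a matter of judgement, the top rows of the table are more plausible than the bottom ones.

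**Chance imbalance in disease status.** If sex were the only stratum, a hypergeometric calculation gives a 20% chance of an 18:12 or worse split of each disease group between arms, and 7% for 19:11 or worse. It is tempting to cite these figures. But they need the less natural reading of the allocation sentence, and they ignore blocking and recruitment order. Allowing for both, with the last 10 participants all impaired, gives about 12% and 4%.

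**A journal article is condensed.** A full covariate list may stand in a document not shown. This lowers the weight of the point but does not remove it: the article does state its tests and a covariate rule, and that rule omits the named stratum.

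**Conclusion.** The point holds in a limited form. Sex is a stated stratification factor, no stated test or model includes it, and the only covariate rule concerns age. Any verum–sham comparison is then conservative to the extent that sex predicts the pre–post change, and the same applies to disease group where the two groups are pooled.

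The size rests on an assumed R². For sex within one disease group of 30, it is nil at 0.02 or less, 2–3 points of power at 0.05–0.10, and 7–13 points at 0.20–0.30. If sex is not prognostic there is no loss. The error runs in the safe direction, so the documents do not support a reading that the comparison is invalid or its type I error inflated. Severity is minor: this is a nearly free improvement.

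**What to change.** - In Statistical Analysis, specify the between-arm model for the pre–post imaging outcome with arm, sex, the pre-needling value and, whenever the disease groups are pooled, disease group as fixed terms. Include them regardless of observed balance.
- If pre and post values are both kept as outcomes in a mixed model, let sex and disease group interact with time. A main effect alone does not sharpen the comparison of changes.
- In Enrollment, Randomization, and Blinding, state whether disease group was a randomisation stratum. If lists were by sex only, say so and rely on the adjustment.

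The cost is one or two degrees of freedom for the strata and one for the baseline value, all from data already collected, plus one clarifying phrase. In the simulations, strata that predict nothing cost almost no power: 0.802 against 0.806 with 30 participants, and 0.79 either way with 60.
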